### Trial design and study arms

#### Trial design

This study will be a cluster randomised controlled trial. This design is applicable as it allows for a field-based intervention to be implemented for one competitive season while decreasing the chances of contamination between the groups. African women’s football is the sport that has been chosen as it is the most commonly played women’s team sport on the continent and therefore, is a priority sport for improving medical care at and from grassroots levels. Adherence to the FIFA Football Nurse program; football exposure data; injury, illness and medication use surveillance and the in this trial will be similar to those used in previous football studies [35, 37] and conform with the definitions and data collection procedures outlined in the latest injury consensus statements [36]. The study will also include a qualitative evaluation of the participants’ (players, coaches, nurses) experience of the FIFA football nurse program.

All the 24 women’s teams in the Malawi Women’s Super league will be randomly assigned in a 1:1 ratio to either the Football Nurse intervention (INT–12 teams) or the control group/standard care (CON–12 teams) through a random draw. For the allocation schedule for random assignment to each arm, the names of the 24 teams will be placed in three (3) bowls, a bowl for each region. They will then be picked consecutively and alternately, and allocated into the INT and CON groups by one of the investigators ([name]). This will be done after the training of the nurses and after each team (cluster) have agreed to be a part of the study. For transparency, the random draw will be conducted in the presence of representatives from the football association and will be video and audio- recorded.

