#### Sample size

The study aims to evaluate the impact of the Football nurse intervention on team sports medicine practice. Hence, the study will recruit twelve (12) nurses, with one assigned to each intervention team, and six (6) physiotherapists and/or doctors to supervise the Football Nurses from two teams each.

To determine the appropriate sample size, the study used the cluster randomized formula as in previous studies [38]. This formula considers the intra-cluster correlation coefficient, number of participants, expected effect size, and power of the study. The formula is as follows:

$$C=1+{\left(Z_{\alpha /2}+Z_{\beta }\right)}^{2}\frac{\left[\sigma_{0}^{2}+\sigma_{1}^{2}\right]\times [1+(m-1)k]}{m{\left(\mu_{0}-\mu_{1}\right)}^{2}}$$

Where C is the number of clusters required per treatment arm, *Z*_*α*/2_ and *Z*_*β*_ are the critical values of the standard normal distribution for the desired confidence level and power, respectively, *m* is the number of individuals per cluster and *k* is the intracluster coefficient, *μ*_1_ and *μ*_0_ are the true means, and σ_1_ and σ_0_ are the standard deviations, of the outcome variable in the presence and absence of the intervention, respectively.

The design effect of a CRT is related to the intracluster correlation coefficient as follows:

DEFF=1+(m−1)k

Assuming a 95% confidence level (*Z*_*α*/2_ = 1.96), a power of 80% (*Z*_*β*_ = 0.84), an expected effect size of 0.19 (based on a 50% increase in team sports medicine practice), a standard deviation of 0.30, an intra-cluster correlation coefficient of *k* = 0.2, and 25 participants per cluster, the study estimates that it will need 12 clusters (teams) in both the control and intervention groups. Therefore, a total of 600 participants will be recruited, with 300 participants in each group. In summary, the study will recruit twelve (12) nurses and six (6) physiotherapists/doctors to supervise the intervention teams. The study will need 12 clusters (teams) in both the control and intervention groups, with a total of 600 participants (300 in each group) to detect a statistically significant change in team sports medicine practice at a 95% confidence level and 80% power, using the cluster randomized formula [38, 39].

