#### Recruitment

The 24 teams that will be targeted for this intervention compete in the Malawi Super League, which is the highest organised league for women’s football in Malawi. The level of football is amateur, as is most women’s football in LMICs. However, the league produces many of the players for the national teams. The teams in the league are divided into eight (8) teams each by geographical region into the Northern, Central and Southern regions. The distribution of teams into the two arms per region is shown in **Fig 2** below.

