In the event of a participant being flagged as being at risk of self-harm or harm to others in the mental health screening, the Football Nurses and their supervisors will be obliged to provide brief intervention within the scope of their practice, following which they will refer the participant for further management by the relevant healthcare providers. Should a medical condition be detected in the physical assessments, a similar approach will be taken in the management of the player.

*Data analysis*. Data will be analyzed using the IBM Statistical Package for Social Sciences (SPSS) version 21. The Shapiro-Wilk test for normality of the data will be conducted. Baseline comparability of participants for potential confounding factors such as age, length of football career, and baseline injury risk will be conducted using a chi-square test (for categorical variables) and either independent t-tests [normally distributed data] or Mann-Whitney U tests [non-normally distributed data] (for continuous variables).

Due to the relatively small number of clusters, data analyses will be based on summary level measures to account for the shortcomings of individual level regression methods. The primary variable of interest will be sports medicine practice. The mean (SD) sports medicine practice score will be calculated and presented by cluster and by arm. The mean of these mean scores and their associated 95% confidence intervals (CI) will then be presented for each arm. Linear regression of the mean sports medicine practice scores per cluster and per arm; two-way analysis of variance (ANOVA), will be used to explore the differences in sports medicine practice score and the 95% CI associated with the FIFA Football Nurse intervention by arm.

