For the testing data such as injury risk (FMS, musculoskeletal screening), nutritional data (24h recall), and mental health assessment (SMHART-1), a mixed between-within-subjects ANOVA will compare the two arms over the whole intervention, then a post hoc Bonferroni test will be used to determine whether there are significant changes in the various scores and at what time point during the intervention these occur. Should there be a significant change in test scores, a one-way ANOVA will be performed at the specific time point to determine which specific test is different between arms. Additionally, a mixed effects logistic regression model will be used to examine the effects of arm assignment (intervention vs control) and time for categorical outcomes (e.g., sports injury prevention behaviours). To assess adherence and feasibility, descriptive statistics will be used to determine which aspects of the FIFA Football Nurse programme are best or worst implemented. Sensitivity analyses include adjustment for baseline team sports medicine practice and other potential confounding factors (e.g., previous injury, age, football experience, BMI, socioeconomic status). We will also include tests for effect-modification by relevant factors.

Additionally, data from the semi-structured interviews will be transcribed verbatim and a thematic analysis will be conducted using Braun and Clarke’s 6 step model [44] to group common themes and describe the experiences of women’s football stakeholders, and the barriers and facilitators towards the football nurse task-sharing approach. Analysis will be approached inductively by tagging meaning units which will then listed as themes, compared, and clustered to form categories, then assigned as general dimensions. Inter-rater reliability checks will be conducted by a blinded researcher, who will code a subset of the manuscripts and determine congruence of resulting themes. If clustering effects are observed in the data, these will be accounted for using appropriate statistical methods such as multilevel or hierarchical models.

All statistical tests conducted in this trial will be two-sided and p-values of < 0.05 will be considered statistically significant.

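### The primary two-way ANOVA has no usable second factor: team is nested in arm, and region, the stratum of the draw, is not named

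*Protocol article*

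**What the plan says.** The Data analysis paragraph of the protocol article (under Secondary outcome measures) bases the analyses on cluster summaries because there are few clusters. It has the mean practice score tabulated for each cluster and each arm, and then gives the primary comparison: "Linear regression of the mean sports medicine practice scores per cluster and per arm; two-way analysis of variance (ANOVA), will be used". The factors of the ANOVA are not stated anywhere else.

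Under Trial design, teams are "randomly assigned in a 1:1 ratio to either the Football Nurse intervention (INT–12 teams) or the control group/standard care (CON–12 teams", so a team belongs to one arm only. For the draw, "the names of the 24 teams will be placed in three (3) bowls, a bowl for each region". The Recruitment section adds: "The teams in the league are divided into eight (8) teams each by geographical region". Names are then picked alternately for the two arms, which gives four teams per arm in each region.

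Region does not appear in the primary model. It is also absent from the covariates listed for the injury models and for the sensitivity analyses.

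The planning values under Sample size are "an expected effect size of 0.19 (based on a 50% increase in team sports medicine practice"), "a standard deviation of 0.30", an intracluster correlation of 0.2, "and 25 participants per cluster, the study estimates that it will need 12 clusters (teams) in both the control and intervention groups". On testing: "All statistical tests conducted in this trial will be two-sided and p-values of < 0.05 will be considered statistically significant".

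**The concern.** This sentence defines the trial's one primary comparison, made on 24 units. An analyst who follows it has to supply the second ANOVA factor. The factor that the wording suggests, team, cannot be used, because arm is a function of team. The factor that the design suggests, region, is not mentioned.

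Two things are at stake. First, the primary p-value and interval cannot be reproduced from the text, because more than one model fits the wording. Second, if the analyst falls back on arm alone, between-region differences stay in the error term although the draw has already balanced them across the arms. The standard error then overstates the uncertainty of the arm difference.

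**Working it through.** **The plan's own figure.** Sample size formula with 1.96 + 0.84 = 2.80, SD 0.30, m = 25, k = 0.2, difference 0.19:
- DEFF = 1 + 24 × 0.2 = 5.8
- C = 1 + 2.80² × (2 × 0.09) × 5.8 / (25 × 0.19²) = 1 + 8.185 / 0.9025 = 10.07, so 11 teams per arm

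The article states 12. The difference is on the safe side and does not bear on this point. The rest uses 12 per arm.

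**Team plus arm on 24 team means.** The design matrix has 1 (intercept) + 1 (arm) + 24 (teams) = 26 columns and rank 24. Residual df = 24 − 24 = 0. The arm column is a sum of team columns, so its effect is aliased and there is no error term.

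**Arm alone on 24 team means.**
- Rank 2, residual df 22, t critical value 2.074
- Team-mean variance V = 0.09 × 5.8 / 25 = 0.02088 (SD 0.1445)
- SE of the arm difference = √(2V/12) = 0.0590; noncentrality 0.19 / 0.0590 = 3.22
- Power 86.8%; simulated size 5.1% when region has no effect

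**Arm plus region on 24 team means.** Rank 4, residual df 20, t critical value 2.086. With no region effect, power is 86.5% and simulated size 5.1%.

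**When region matters.** The article does not say how strongly region predicts the score, so the share R of team-mean variance is an assumption. Take fixed region effects, with within-region variance σ² = (1 − R)V and region variance τ² = RV. The draw balances arms within region, so the true SE of the arm difference is √(σ²/6) under either model. With region omitted, the expected residual mean square is σ² + 24τ²/22.

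| R | 95% half-width, arm only | 95% half-width, arm + region | Ratio |
|---|---|---|---|
| 0.2 | 2.074 × √(0.02126/6) = 0.1234 | 2.086 × √(0.01670/6) = 0.1101 | 1.12 |
| 0.3 | 2.074 × √(0.02145/6) = 0.1240 | 2.086 × √(0.01462/6) = 0.1030 | 1.20 |

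Separate simulations put these ratios at 1.12 to 1.13 and 1.21 to 1.22.

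| R | Size, arm only | Size, arm + region | Power at 0.19, arm only | Power at 0.19, arm + region |
|---|---|---|---|---|
| 0.2 | about 3% | 5% | 89% | 93% |
| 0.3 | about 2% | 5% | 90% | 96% |

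**Variant with random region effects.** Suppose region carries 25% or 50% of the between-team component (0.2 × 0.09 = 0.018). Arm-only size is then 3.6% or 2.2%. Power is 90% against 94%, or 93% against 98%. The direction is the same.

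**The case against.** The best defence is that the sentence already contains a valid analysis. The wording about cluster and arm may describe only how the means are summarised, since the preceding sentences use a similar phrase for tabulation. On that reading the test is a linear regression of team means on arm, which holds its 5% level. A two-way ANOVA of team means by arm and region would also be sound and may be what was intended. This stands, and it means the planned primary result cannot be called invalid. It does not supply the missing factor: the sentence says two-way and does not name a second classification that works.

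It can also be said that a condensed article may leave the stratum covariate to an analysis plan that is not shown. That is fair for region taken alone. But the article does fix a primary model, and the model as worded is the problem.

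A reader might infer more than the text supports:
- **Gross inflation of false positives**, near 47% at k = 0.2 and m = 25 (mean-square ratio (0.8 + 25 × 0.2)/0.8 = 7.25). This needs player-level scores with arm tested against within-team error. The Data analysis paragraph calls for summary measures, and the Introduction makes the team the unit of analysis, so the article rules this out.
- **Inflation to about 16%**, from treating three visits as independent in an arm-by-time ANOVA. The primary paragraph names no time factor, and the figure assumes a between-visit correlation of 0.5. Where the article compares arms over time, for other outcomes, it specifies a mixed between-within ANOVA.
- **A false-positive risk from omitting region.** The effect runs the other way: the test becomes conservative.
- **An underpowered primary test.** At the stated difference of 0.19, arm-only power is above the 80% target in every case examined.

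**Conclusion.** The point holds as a defect of specification. Read literally, the two-way ANOVA has team as its second factor, leaves 0 residual df and gives no arm effect. Read charitably, its second factor is undefined. The regression on arm alone is valid but ignores the strata of the draw.

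The cost of ignoring them depends on how far region predicts the score, which the article does not say. At an assumed 20 to 30% of team-mean variance, the interval is about 12 to 22% too wide, the size about 2 to 3% instead of 5%, and power at 0.19 about 89 to 90% instead of 93 to 96%. At 0% the two models are practically equal (86.8% and 86.5%). These figures rest on the protocol's SD, intracluster correlation and cluster size, 12 teams per arm, and four teams per arm in each region. The documents do not support the broader conclusion that the primary result would be wrong or not estimable.

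**What to change.** Replace the sentence with: the 24 team-level practice scores will be analysed by one linear regression on arm and region (three levels), equivalently a two-way main-effects ANOVA of arm and region. The adjusted mean difference will be reported with a t-based 95% confidence interval on 20 residual degrees of freedom. Remove any ANOVA that has team as a factor.

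The cost is one sentence and two degrees of freedom (t 2.086 instead of 2.074), or about 0.3 percentage points of power if region proves irrelevant. The practice score is measured at three time points. Which of them supplies the primary score is a separate decision that this change does not settle.

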#### Control or standard care

In the control or standard care group (CON) consisting of 12 teams (clusters), each team will have 30 registered players, one (1) team manager, and one (1) coach and will continue their SEM practise ‘as per usual’. A member of the research team will contact a designated member of their technical personnel to collect data on football exposure; injury, illness and medication use surveillance after each training session and league match. Beyond this, the teams in the CON group will not receive any special instructions. It is noteworthy that the teams in the CON and INT groups will at some point in the season play against each other and the Football Nurse will be duty bound to render care should a player from the CON group be injured or fall ill during the match. Therefore, contamination cannot be entirely avoided.

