#### Standardisation of procedures

The physiotherapists and doctors will complete the modules from the freely and publicly available online FIFA Medical Diploma before the trial commences. This will allow for uniformity of football medicine practice and supervision among the participants during the trial. Shortly before the football season begins (1 week before), all the nurses and the physiotherapists/doctors will undergo a one (1) day training on emergency pitch side football medicine using the latest version of the FIFA Emergency Care training manuals. This training will be conducted by experienced sports medicine personnel ([name] and EC) as well as experienced trainers in basic life support (BLS) and first aid from the Departments of Emergency and Orthopaedics at KUHeS. Further, all research personnel will receive half a day’s training on the online data capturing system that will be used for the study. The research team will have access to written standard operating procedure on their mobile data collection devices as well. The team will also meet every fortnight to catch up and ensure adherence to standard research procedures.

The football nurse attached to each team will be primarily responsible for data collection for the INT teams and the research team, through a designated individual in the football team, will be responsible for data collection for the CON teams.

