*Adherence*. This study has been designed to be optimally implemented in grassroots women’s football in a low-income setting. The researchers will monitor adherence of the nurses’ attendance at training sessions and matches using electronic record sheets. These records will then allow for exposure hours to be calculated and a measure of adherence to be determined. The surveillance data will be monitored on a biweekly basis to ensure it is up to date and following standardised operating procedures. The study is being performed in a league that has massive shortages of medical personnel and therefore, the participants in the intervention group will be motivated to adhere to the protocol as best they can.

*Ethical considerations*. Permission was sought and obtained from FAM and Directors of District and Social Services (DHSS) in all the regions where the women football teams are based. Ethical approval for this trial was obtained from the College of Medicine Research and Ethics Committee (COMREC), Blantyre, Malawi (protocol number: P.01/22/3551). The study will be conducted in accordance with the Declaration of Helsinki, the protocol and GCP guidelines. Before they can be a part of the study, and before randomisation, the investigators will explain the objectives of the study to the physiotherapists, doctors and nurses; football teams, their women players, and their coaching teams. They will only then be eligible to be included in the randomisation and eventual participation in the study after they have provided verbal and written assent and consent. This study will be voluntary, and participants will be informed that they have a right to participate or to withdraw from the study at any time, without prejudice. Data collected from the study will be stored in a password protected database and computer and that will only be accessible to the researchers. Study participants will be assured of their confidentiality. The names of the participants will only be on the consent form and in all other instances, they will be referred to by their assigned unique code.

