For the injury, illness, and medication use data, injury, illness, or medication use history will be recorded to determine the baseline injury, illness, or medication use risk. Injury, illness, and medication use rates and corresponding 95% CIs will be calculated for all players as the number of injuries/illnesses/medications reported per 1000 hours of football exposure (training and match). The severity of the injuries/illnesses, as scored by the number of days of missed training or matches, will also be calculated. Additional analysis will include, but not be limited to, the incidence and type of injury/illness/medication; chronic versus acute injuries/illnesses/medications; contact versus non-contact injuries and mechanism of injury (all per 1000 player hours). A Poisson regression will be used to compare differences in the injury, illness, or medication use rates between the control and intervention arms. To evaluate the impact of the FIFA Football nurse intervention on injury/illness/medication use outcomes, we will use logistic regression analysis to compare the proportion of players with injuries/illness/taking medications between the intervention and control arms, adjusting for potential confounding variables such as previous injury, age, playing experience, BMI, and playing conditions. We will also conduct subgroup analyses to determine whether the intervention has differential effects on different subgroups of players.

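### Illness and medication rates are divided by football hours, which are not the time at risk for either, so unequal hours between arms can distort the Poisson rate ratios

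*Protocol article*

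**What the plan says.** The Data analysis paragraph (under Secondary outcome measures in the protocol article) sets one denominator for three kinds of event: "the number of injuries/illnesses/medications reported per 1000 hours of football exposure (training and match". The additional breakdowns, which include type of illness and of medication, use the same scale: "contact versus non-contact injuries and mechanism of injury (all per 1000 player hours". The test between arms follows: "A Poisson regression will be used to compare differences in the injury, illness, or medication use rates between the control and intervention arms". No denominator in player-days, player-weeks or seasons is given anywhere for illness or medication.

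The same paragraph plans a second comparison that does not use hours: "we will use logistic regression analysis to compare the proportion of players with injuries/illness/taking medications between the intervention and control arms".

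On who records the data, Standardisation of procedures says "The football nurse attached to each team will be primarily responsible for data collection for the INT teams". For control teams, Control or standard care says that research staff "will contact a designated member of their technical personnel to collect data on football exposure; injury, illness and medication use surveillance". The Adherence paragraph, after describing electronic records of the nurses' attendance, adds "These records will then allow for exposure hours to be calculated and a measure of adherence to be determined". The Football exposure paragraph, however, has exposure collected on injury, illness and football load forms.

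**The concern.** A rate needs the time at risk as its denominator. For injury, training and match hours serve well. A player can fall ill or take a medicine on any day, whether or not she trains, and calendar time under surveillance is planned to be the same in both arms. Football hours need not be the same, for three reasons.

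- They arise after randomisation. A nurse who assesses, treats and refers players may change how much they take part, so a per-hour rate ratio mixes an effect on participation with an effect on illness.
- Illness can lower hours. The plan scores illness severity by missed training or match days, so it accepts that ill players miss sessions. If the hours of absent players are left out, equal illness and equal absence in both arms would cancel in the ratio. Different absence for the same number of illnesses would not.
- Different people record them: the nurse in one arm, a team contact in the other.

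At stake is the comparison of illness and medication incidence, a named secondary objective. An apparent nurse effect could appear, or a real one be hidden, because one arm played more or logged its hours more completely.

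**Working it through.** The documents give no illness rate, medication rate or expected hours, so there is no figure of the plan's own to reproduce. The check is algebra with assumed values.

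**Inputs from the protocol article.** Surveillance runs from June to December 2022, about 7 months, in both arms (Project time frame). There are 300 participants per arm, 12 teams of 25 (Sample size); 30 registered players per team would give 360. Tests are two-sided at 0.05 (Data analysis).

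**Assumed inputs.** The ratio of intervention to control hours, h, runs from 0.8 to 1.25. Events run from 0.05 to 0.2 per player-month.

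**Step 1, the upper case.** Let recorded events per player-day be equal in the two arms and unrelated to hours. Then

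per-hour rate ratio = (events ratio) / (hours ratio) = 1/h.

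- h = 1.2: 1/1.2 = 0.83
- h = 1.1: 1/1.1 = 0.91
- h = 0.9: 1/0.9 = 1.11
- h = 0.8: 1/0.8 = 1.25

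**Step 2, allowing events to follow sessions.** Surveillance is logged after each session or match, so an arm that logs more sessions may also capture more events. Let recorded events rise as h to the power a, with a between 0 (unrelated to hours) and 1 (fully proportional). The per-hour ratio is then h^(a−1) and the player-day ratio is h^a.

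| h | a | per-hour ratio | player-day ratio |
|---|---|---|---|
| 1.2 | 0 | 0.83 | 1.00 |
| 1.2 | 0.5 | 0.91 | 1.10 |
| 1.2 | 1 | 1.00 | 1.20 |
| 0.8 | 0 | 1.25 | 1.00 |
| 0.8 | 0.5 | 1.12 | 0.89 |
| 0.8 | 1 | 1.00 | 0.80 |

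So 1/h is the limit of the distortion, reached only at a = 0. The table also shows the cost of a player-day rate when recorded events follow sessions.

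**Step 3, chance of a false positive in the upper case.** With E = players × 7 × rate events per arm, the standard error of the log rate ratio is √(2/E), ignoring clustering. For 300 players and 0.1 events per player-month, E = 300 × 7 × 0.1 = 210 and the standard error is √(2/210) = 0.098. At h = 0.8, ln(1.25) = 0.223, and 0.223/0.098 is about 2.29. The chance of p < 0.05 is then 63%. With 300 players per arm:

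- h = 0.8 or 1.25: 37%, 63% and 90% at 0.05, 0.1 and 0.2 events per player-month
- h = 1.1: 11%, 16% and 28%

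With 360 per arm, h = 0.8 or 1.25 gives 43%, 71% and 94%. All these figures take a = 0 and are upper cases in that sense.

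**The case against.** The strongest reply has five parts.

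**There is another analysis.** The logistic comparison of proportions covers the same outcomes and does not divide by hours. This stands, and it limits the reach: a reader might infer that the whole illness and medication comparison is compromised, but only the rates and their Poisson test are. The logistic result does not correct the Poisson result, though, and the article does not say how to read the two if they disagree.

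**Capture is driven by sessions.** A reader might infer that any difference in hours passes in full into a false difference in illness. The documents do not support that. Events are logged at sessions, so the count may move with hours, and some medication use follows football injury. This stands, and it makes 1/h an upper limit.

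**The source of intervention hours.** It is tempting to say that these hours come from nurse attendance records while control hours come from elsewhere. The Adherence paragraph can be read that way, but the Football exposure paragraph names load forms, and the Adherence text may concern only the nurses' own adherence. Different recorders by arm are documented; a different kind of source is not clearly so. Likewise, exposure is said to be collected at cluster level, and whether an absent player's hours are dropped is not stated, so illness reducing its own denominator is possible rather than established.

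**No gap in hours is documented.** All teams play in one league and season, and allocation is drawn within region, which makes a large gap in match hours less likely. Training hours and completeness of recording could still differ.

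**The remedy has a mirror problem.** If recorded events rise fully with sessions, the player-day ratio is h rather than 1. This stands as a limit of the fix. It does not make football hours the time at risk.

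**Conclusion.** The point holds in a limited form. The article fixes football hours as the denominator for illness and medication rates and tests those rates between arms. Hours are not the time at risk for either outcome, they arise after randomisation, and they are recorded by different people in each arm, so a difference in hours can distort the two rate ratios.

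Given equal incidence per player-day and otherwise equal capture of events, the distortion lies between none and 1/h: up to 0.83 for 20% more intervention hours, up to 1.25 for 20% fewer. The hours ratios and event rates are assumptions, and nothing in the documents shows that gaps of this size will occur.

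Injury rates per 1000 hours are sound on this point. The logistic comparison, the team sports medicine practice score and the sample size are untouched. The abstract lists injury and illness incidence within its primary objective, but the Primary objective, Primary outcome measure and Sample size sections all rest on team practice, so this remains a matter of secondary outcomes.

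**What to change.** Keep rates per 1000 hours for injuries. For illness and medication use, make player-time under surveillance the Poisson offset: each registered player's days or weeks from the June start to December, ending when she leaves the team where that date is known. Define it identically in both arms and report rates per 1000 player-days. Give the per-hour rate as a supplementary figure; if the two differ materially, that shows how far the result depends on hours.

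The cost is a change of analysis wording plus, possibly, a note of the date when a player leaves, since the article does not say that these dates are collected. The new offset removes the artefact of unequal hours. It does not correct differences between arms in how completely illnesses and medicines are recorded, and the report should say so.
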